### Group allocation

Participants will be randomized using a single, constant 1:1 allocation ratio determined with web-based software (http://www.sealedenvelope.com). Selection criteria will be checked prior to participation in the study.

### Confidentiality

Information about study subjects will be kept confidential. All data will be entered into the REDCap data management system where all data on study participants are assigned an individual identifying code that does not contain identifying information. Only anonymized data will be submitted as part of the statistical analysis. No direct or indirect personal participant’s study information will be released outside of the study without his/her written permission. Individual performance during the resuscitation scenario will remain confidential and will not be communicated at the institutional level.

### Statistical analyses

For the primary outcome, 48 subjects completing two scenarios each will provide a total of 96 SAGAT and 16 TSAGAT scores for analysis. For each query, two study investigators will score the answers. In the case of disagreement, a third investigator will find a consensus. The normality of variable distributions will be examined with the Shapiro-Wilks test. For normally distributed variables, means and SDs with 95% confidence intervals (CI) will be reported and scores compared between intervention groups using Generalized Estimating Equations (GEE) to account for the cluster randomized design. Non-normally distributed variables will be reported with medians and interquartile ranges.

For the secondary outcomes, each of the three SAGAT domains will be compared between the intervention groups using GEE for each scenario. We will also compare SAGAT scores according to the team members’ roles. Regarding the RTLE and TEAM instruments, differences between the two intervention groups will be assessed using multinomial logistic GEE for the single items, and linear GEE with an identity link for the sum score, and the global rating performance.

Kaplan–Meier curves for the time elapsed between the end of the clinical statement by the study investigator and timed secondary outcomes will be compared using the log-rank (Mantel-Cox) test including a cluster term to account for the cluster randomized design. Wrong defibrillation or drug doses will be measured as a deviation from the amount of energy delivered in Joules or drug doses in milliliters compared to 2018 AHA PALS cardiac arrest algorithm, respectively. Use of epinephrine 0.1 mL/kg (0.1 mg/ml concentration) and amiodarone 5 mg/kg (150 mg/3 mL concentration) are expected for the first scenario. We define an emergency medication dose administration error as a deviation from the correct weight dose of more than 10% [55]. Moreover, defibrillations (in Joules) and the number of shocks will be also measured during the first scenario. Defibrillation doses of 2 J per kg for the first attempt and 4 J per kg for the subsequent second, third and fourth attempts are expected [5]. A GEE model with a Poisson link will be used to assess the relationship between absolute errors in defibrillation and drug doses expressed as categorical variables. Wrong defibrillation mode will be also measured. Absolute deviations will be analyzed. The mean (SD) difference obtained with each intervention method will be reported with a 95% CI. Univariable linear GEE with 95% CI will be performed to assess whether time to initiation of chest compression, defibrillation attempts, and drug delivery are associated with prior resuscitation experience as a clinician in real-life and simulated environments. Similar analyses will be carried out for errors in fluid resuscitation volumes (in milliliters) and blood transfusion during the second scenario. An initial 20 mL/kg bolus of isotonic crystalloid followed by 10–20 mL/kg of packed red blood cells and 10–20 mL/kg of fresh frozen plasma and platelets are expected [40].

A first rater (one of the study investigators) will review all videos. To assess the reproducibility of the video review procedure, a second reviewer will independently duplicate the review in a random sample of 20% of all videos. Interrater reliability scores on video reviewing will be calculated using Cohen’s kappa coefficient for categorical variables. We define poor reliability as a kappa coefficient of < 0.4, fair reliability as 0.4–0.6, good reliability as > 0.6–0.8, and excellent as > 0.8. Any disagreements in video reviewing will be resolved by a third independent investigator, including appropriate revision of the implemented reviewing strategy, followed by double-reviewing of a further 10% until reliability on video reviewing (a kappa of 0.6 or greater) is achieved. For continuous variables, the Bland-Altman method will be used to plot the difference of values reported by both reviewers against the mean value for each outcome. The limits of agreement will be assessed by the interval of ± 1.96 SDs of the measurement difference on either side of the mean difference. The null hypothesis that there is no difference on average between both reviewers will be tested using a *t* test. The mean difference will be reported with its 95% CI. Additionally, the intraclass correlation coefficients for the volumes of drugs drawn, time to drug preparation, and time to drug delivery will be assessed, assuming that raters are a sample from a larger population of possible raters.

Finally, means and SDs will be determined for perceived stress and satisfaction scores of participants for each scenario, as well as for the SUS questionnaire, and reported with descriptive statistics. In the case of missing data, a complete case analysis will be conducted. No multiple imputations are planned. All statistical tests will be two-sided with a type I error risk of 5%. Data analysis will be performed using GraphPad Prism, version 7 (GraphPad Software, San Diego, CA, USA) for graph figures, and R version 4.0.4 (R Foundation, Vienna, Austria) for descriptive statistics and statistical tests.

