### Power and sample size calculation

A previous study found a 23.5% SA improvement in intensive care unit nurses exposed to an integrated information display compared to a traditional display exposure [54]. In this trial, the sample size was calculated to provide 90% power at a two-sided alpha level of 5% in detecting a relative difference of at least 25% SA improvement between intervention groups, with an assumed standard deviation (SD) set at 0.2. This SD is based on and conservatively about twice as much as that observed by Koch et al. [54]. The required sample size is 14 participants per study arm. To prevent a potential loss of power due to misspecification of assumptions, 18 participants (= 3 teams of 6 people per team) should be recruited per randomized group. To take into account the cluster randomized trial design, this sample size was inflated using a variation inflation factor of 1.25 (= 1 + 0.05(6–1); 0.05 being the intraclass correlation coefficient). The total sample size (i.e., 45 participants) was finally rounded up to 48 participants to obtain 8 teams of 6 participants per team.

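### The primary GEE comparison rests on 8 teams with no small-sample correction named; under standard GEE inference the stated 5% type I error would be about 14%

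*Protocol article*

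**What the plan says.** In the protocol article, Power and sample size calculation gives a total that was "finally rounded up to 48 participants to obtain 8 teams of 6 participants per team". Group allocation adds: "Participants will be randomized using a single, constant 1:1 allocation ratio". It does not write out how many teams go to each arm and mentions no blocking.

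Statistical analyses says that "48 subjects completing two scenarios each will provide a total of 96 SAGAT and 16 TSAGAT scores for analysis". Means and SDs of normally distributed variables are reported with 95% confidence intervals, and "scores compared between intervention groups using Generalized Estimating Equations (GEE) to account for the cluster randomized design". For RTLE and TEAM, "differences between the two intervention groups will be assessed using multinomial logistic GEE for the single items", with linear GEE for the sum scores and the global rating. The section closes its testing rules with "All statistical tests will be two-sided with a type I error risk of 5" percent.

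The article names no variance estimator, working correlation, reference distribution, team-level test or permutation test. The only provision for clustering in the sample size is a design effect of 1.25, from an ICC of 0.05 and teams of 6.

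**The concern.** The usual GEE test divides the estimate by a sandwich standard error and refers the ratio to a normal distribution. Both steps are justified for many clusters. With four teams per arm the sandwich variance is biased downward, and it is itself estimated from only six between-team degrees of freedom. The design effect allows for correlation within teams but not for this shortage of teams.

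The primary endpoint is at stake. A significant SAGAT result could carry nearly three times the advertised false-positive risk, with an interval that looks more precise than it is. The other linear GEE comparisons (TSAGAT, RTLE and TEAM sum scores) rest on the same 8 teams. The single-item multinomial models face a separate difficulty, which is too few ratings to fill the response categories.

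**Working it through.** **Inputs.** 8 teams of 6, 1:1 allocation, difference 0.25, SD 0.2, ICC 0.05, 90% power, two-sided 5% (Power and sample size calculation; Group allocation; Statistical analyses). The 4/4 split is inferred from 8 teams at 1:1.

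**The plan's own sample size.** n per arm = 2 × (1.960 + 1.282)² × 0.2² / 0.25² = 13.45, so 14, as stated. Then 2 × 18 × 1.25 = 45, rounded up to 48. The figure reproduces when 0.25 is taken as an absolute difference on the scale of the SD. The fault is therefore not in the arithmetic of the total.

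**Size of the standard GEE test.** With k equal teams per arm and between-team variance s² of the team means:
- The unbiased variance of the arm difference is 2s²/k.
- The uncorrected sandwich variance is (k − 1)/k times that, so 3/4 of it for k = 4.
- The Wald z test therefore rejects when |t| on 2k − 2 = 6 df exceeds 1.960 × √(3/4) = 1.697.
- Type I error = 2 × P(t₆ > 1.697) = 0.1405, so coverage is 1 − 0.1405 = 0.86.
- The valid critical value is 2.447. The interval width ratio is 1.697 / 2.447 = 0.694, about 31% too narrow.

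**Simulation check** (8 teams × 6 members × 2 scenarios, no treatment effect, 2,000 runs per setting unless noted). Robust standard errors rejected in 13.75% to 15.3% of runs across ICC 0, 0.05 and 0.2, with exchangeable or independence working correlation. Model-based standard errors with an estimated exchangeable correlation gave 13.9% to 15.4%.

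**Partial corrections.**

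| Variance and reference | Type I error |
|---|---|
| Uncorrected sandwich, normal | 14.1% |
| Unbiased variance, normal | 9.8% |
| Uncorrected sandwich, t(6) | 7.8% |
| Bias-reduced variance, normal | 6.4% by formula (6.2% to 7.2% simulated, 1,000 runs) |
| Unbiased variance, t(6) | 5% by construction |

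**If the split is not 4/4.** The uncorrected test has size of about 15.6% at 3/5 and 22.9% at 2/6.

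**Power with t(6).** SE = √(2 × 0.2² × (1 + 5 × ICC) / 24), one score per participant, difference 0.25:

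| ICC | SE | 0.25 / SE | Power, t(6) | Power, normal |
|---|---|---|---|---|
| 0.05 | 0.0645 | 3.87 | 89.4% | 97.2% |
| 0.10 | 0.0707 | 3.54 | 83.6% | 94.2% |
| 0.20 | 0.0816 | 3.06 | 72.4% | 86.5% |

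The article calls the 25% relative and gives no control mean. If the score is a proportion and the control mean is assumed to lie between 0.5 and 0.8, the difference is 0.125 to 0.20. Power with t(6) at ICC 0.05 is then about 37% to 73%.

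**Single items.** Each arm has 4 teams × 2 scenarios = 8 ratings per item. A TEAM item has 5 categories. Under uniform independent ratings, the chance that 8 ratings fill all five is 5! × 1,050 / 5⁸ = 126,000 / 390,625 = 0.323 (1,050 being the number of ways to split 8 ratings into 5 non-empty groups). The chance of an empty category in at least one arm is 1 − 0.323² = 0.896, about 90%. In a nominal multinomial model, an empty category in one arm gives infinite log-odds estimates.

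**The case against.** The strongest objection is that the article is silent on the point rather than wrong. It does not say that the sandwich variance is uncorrected or that the reference is normal. A condensed article may leave such details to an analysis plan that is not shown, and a correction there would change the figure. This stands as a limit on the wording: 14% is what standard GEE would give, not an established property of this trial's analysis. It does not remove the point. The article fixes the method, the number of teams and the 5% claim together, and with 8 teams the method named does not deliver that claim without a correction.

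A reader might also infer that the item-level models are singular and can give no test at all. For a nominal 5-category item the full robust covariance, for 8 parameters, does have rank at most 6. But the between-arm test needs only the 4 × 4 treatment block, which had full rank in 290 of 300 simulated data sets with no empty category. The argument also assumes a nominal model for TEAM items. A cumulative-logit model has 5 parameters, and a 4-category RTLE item has 6. What remains is the empty-category problem, and it concerns secondary items only.

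Finally, it is tempting to say that the correction costs no power. That holds only under the conditions shown in the working.

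**Conclusion.** The point holds in conditional form. With 4 equal teams per arm, an uncorrected sandwich variance and a normal reference, the two-sided type I error would be 14.1% against a stated 5%, and the 95% interval would have 0.694 of its valid width. The result hardly depends on the ICC or the working correlation. It does depend on the inferred 4/4 split, and less balanced splits make it worse. The planned total is computed correctly from its inputs, so the weakness lies in the inference method and not in the number recruited. For the single items, the supportable conclusion is that multinomial estimates would often be infinite or unreliable, not that no test could be computed.

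**What to change.** In Statistical analyses, state that the primary SAGAT comparison and the other linear GEE comparisons (TSAGAT, RTLE and TEAM sum scores) use a small-sample bias-corrected GEE variance, for example Kauermann-Carroll, with a t reference on (number of teams − 2) = 6 df. For complete teams of equal size this is equivalent to a t-test on team means. A permutation test over the allocations actually possible is an optional check. There are 70 of these only if a 4:4 split is forced, so the number of teams per arm should be written out.

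Report the TEAM and RTLE single items in descriptive tables instead of multinomial GEE.

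In Power and sample size calculation, say whether the 25% is absolute or relative, and restate the 90% with its conditions: about 89% at ICC 0.05, 84% at 0.10 and 72% at 0.20 for an absolute 0.25 with SD 0.2 and 24 per arm, and lower if the difference is relative.

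The cost is a change of wording and wider intervals. No further recruitment is needed to restore the 5% error rate, but the power claim becomes more modest if the ICC exceeds 0.05 or the difference is relative.

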## Methods/design

### Objectives

The primary aim of this study is to investigate whether the mHealth tool improves SA among team members during standardized, high-fidelity p-IHCA and life-threatening polytrauma simulations. Secondary outcomes are the mHealth tool effect on leadership, team communication effectiveness, and performance compared with conventional communication methods. Our hypothesis is that the use of the tool might improve the above-mentioned non-technical skills, as well as clinical skills, when used by in-hospital emergency teams.

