### Secondary outcomes

#### Leadership

Leadership (domain) will be measured with the resuscitation team leader evaluation (RTLE) instrument (specific measurement) [48]. This instrument developed by Grant et al. encompasses four leadership concepts: (1) the physical and verbal leader’s position, (2) communication and delegating skills, (3) ability to assess, adapt and anticipate, and (4) ability to ask for internal and external help [48]. It comprises 12 items rated on a 4-point Likert scale (metric) from 0 (not performed) to 3 (performed well, consistently) to score leadership and communication skills (Additional file 4). A not applicable (N/A) category is also available for those items not relevant to the scenario. For the purpose of this trial, we will remove items 1 and 12 as the leader will be clearly identified from the beginning of the scenario and teams will not be advised to ask for external help. Therefore, the total item score expressed as an absolute value will range from 0 to 30. Mean overall scores will be aggregated to compare both study arms (method of aggregation). The time frame of interest for this endpoint is over the duration of the whole CPR scenario.

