#### Team performance

Leadership, communication skills, team work, task management, and the team’s overall performance (domains) will be measured as scores obtained from the team emergency assessment measure (TEAM) instrument (specific measurement) [49]. Although a number of tools are available for assessing teamwork performance, the TEAM stands out as the most valid and reliable instrument to use in emergency departments [50]. TEAM comprises 11 items rated on a 5-point Likert scale from 0 (never/hardly) to 4 (always/nearly always), which are summed up into a total item score (metric) expressed as an absolute value ranging from 0 to 44 [49]. The final score obtained allows to assess the performance of the emergency medical team based on three categories: leadership (items 1 and 2); teamwork (items 3 to 9); and task management (items 10 and 11). Items 8 and 9 relate to SA perception and projection, respectively. Furthermore, the team’s overall performance is rated through a twelfth item on a global rating scale of 1 to 10 (higher score denotes better performance) (Additional file 5). Mean overall scores will be aggregated to compare both study arms (method of aggregation). The time frame of interest for this endpoint is over the duration of the whole CPR scenario.

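### Single RTLE and TEAM items are ordered ratings, about 8 per arm from 4 teams, but are to be tested with a multinomial logistic GEE with no ordinal link named, a model these data often cannot support

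*Protocol article*

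**What the plan says.** All places are in the protocol article.

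- **Statistical analyses**, on RTLE and TEAM: "differences between the two intervention groups will be assessed using multinomial logistic GEE for the single items". The same sentence assigns "linear GEE with an identity link for the sum score, and the global rating performance". No link (baseline-category or cumulative), test statistic or rule for empty categories is given for the items.
- **Leadership**, on RTLE: "It comprises 12 items rated on a 4-point Likert scale (metric) from 0 (not performed) to 3 (performed well, consistently"). Of these, "we will remove items 1 and 12", which leaves 10. It adds: "A not applicable (N/A) category is also available for those items not relevant to the scenario".
- **Team performance**: "TEAM comprises 11 items rated on a 5-point Likert scale from 0 (never/hardly) to 4 (always/nearly always"). Items 8 and 9 are linked there to the perception and projection parts of situational awareness.
- **Power and sample size calculation**: the total is "rounded up to 48 participants to obtain 8 teams of 6 participants per team". **Group allocation** fixes 1:1, and **Intervention and resuscitation scenarios** has every team do two scenarios.
- **Objectives**: the hypothesis is directional, that "the use of the tool might improve the above-mentioned non-technical skills".

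**The concern.** The items run from worse to better and the hypothesis is a move towards better. A multinomial logistic model in its ordinary, baseline-category form treats the levels as unrelated labels. Its null hypothesis is that every category has the same share in both arms, so an ordered shift is only one of many departures over which its power is spread.

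The data are also very thin. If a category is used in one arm and never in the other, the log odds ratio for that category is infinite, and a joint Wald test for the item has no valid value. A small-sample correction of the variance does not help, because the estimate itself does not exist. An upward shift tends to aggravate this, since low ratings disappear from one arm.

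At stake are 21 item-level comparisons that show where leadership and teamwork differ, including the two TEAM items tied to situational awareness. Some would come out of the software as very large odds ratios with meaningless standard errors, or as missing results.

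**Working it through.** **1. How many ratings there are.** The plan's own sample size reproduces with a normal approximation if the 25% improvement is entered as a difference of 0.25 with SD 0.2:

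2 × (1.960 + 1.282)² × (0.2/0.25)² = 2 × 10.51 × 0.64 = 13.45, so 14 per arm.

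The plan moves to 18 per arm: 18 × 1.25 × 2 = 45, rounded up to 48, which is 8 teams. At 1:1 this is 4 teams per arm. With one agreed rating per team and scenario (assumed), 4 × 2 = 8 ratings per arm, or 4 if scenarios are analysed separately. N/A ratings can only lower this for RTLE.

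**2. What the model asks of them.** Baseline-category arm parameters: RTLE 10 items × 3 = 30; TEAM 11 × 4 = 44; total 74. One ordered or mean-score effect per item would need 21. Even if ratings were spread evenly, the expected count per category and arm is 8/4 = 2.0 (RTLE) or 8/5 = 1.6 (TEAM).

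**3. Exact check for even, independent ratings.** The chance that all K categories appear in one arm of 8 is Σ(−1)^j C(K,j)(1 − j/K)^8.

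- K = 4: 1 − 4(0.75)^8 + 6(0.5)^8 − 4(0.25)^8 = 0.623; in both arms 0.623² = 0.388.
- K = 5: 1 − 5(0.8)^8 + 10(0.6)^8 − 10(0.4)^8 + 5(0.2)^8 = 0.323; in both arms 0.323² = 0.104.

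**4. Simulation over other distributions.** The protocol gives no distribution of ratings, so this is an assumption and was varied. Settings: 4 teams per arm, 2 ratings per team, latent-normal ratings, within-team correlation 0.05 or 0.5, arm shift 0 or 0.8 SD, 40,000 trials per setting. The entry is the share of items in which a category seen in the trial is empty in one arm, that is, with at least one infinite contrast.

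| Assumed ratings | 4 levels (RTLE) | 5 levels (TEAM) |
|---|---|---|
| Uniform | 59-81% | 84-93% |
| Skewed high | 74-78% | 79-83% |
| Very skewed | 60-68% | 71-73% |
| Centred | not run | 84-91% |
| Nearly all in two categories | 29-46% | 42-45% |

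A second set of runs gave 49-85% with no effect and 49-98% with shifts of 1-1.5 SD. The share usually rises with a shift but not always: for 5 levels with nearly all ratings in two categories it went from 44.8% to 41.6% (correlation 0.05). With 4 ratings per arm the range is about 38-96%.

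**5. Power for an ordered shift of 1-1.5 SD.** A Wald test from the baseline-category model, counting a non-estimable item as no result, reached significance in about 0-13% of items. A two-sample t test on team means (8 − 2 = 6 df) reached about 12-58%, with type I error of 5-6%.

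**6. If a cumulative link was meant.** The arm effect is then infinite when the arms share at most one boundary category. With shifts of 0 or 0.8 SD this happened in about 0-10% of items for spread-out ratings, 1-22% for moderately skewed ones and 12-50% for very skewed 4-level items. In the second set of runs, with an effect present, the range was 5-86%.

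**The case against.** **The link is not stated.** Multinomial GEE can be fitted with a cumulative link, and a condensed article may leave that to an analysis plan. This stands: unordered is the usual reading, not the stated one. But the cumulative reading reduces the problem without removing it (step 6), so the named family suits these data poorly either way.

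**One empty category does not wipe out the item.** This stands too. A reader might infer that most items will give no estimate at all. What was counted is at least one infinite contrast. In a simulation of the same design with no effect, 70-82% of observed categories were on average still used in both arms. Whether even one failure per item is the majority case depends on a distribution the protocol does not give.

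**No Wald test is named.** A generalized score test needs no finite estimate under the alternative. In simulation its power was 2-24% at 1 SD and 7-40% at 1.5 SD, with type I error at or below 5%; the team-mean t test gave 22-34% and 36-59% in those runs. The gain from the t test then runs from about 3 points (concentrated ratings) to about 50 (flat 5-level ratings). It is therefore not always large.

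**The ordered hypothesis is tested elsewhere.** A reader might infer that improvement in leadership and teamwork goes untested. It does not: the sum scores and the global rating have a linear GEE, which uses the order.

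**Conclusion.** The stated item-level model does not fit ordered ratings from 4 teams and 8 ratings per arm, and the sentence should be changed. Under the assumed distributions about 50-85% of items would have at least one infinite contrast with no effect, falling to about 30% when ratings sit mainly in two categories. A Wald-type item test has about 0-13% usable power where a team-mean t test has about 12-58%. The 8 ratings per arm follow from the protocol, given one rating per team and scenario. The percentages rest on assumed rating distributions, within-team correlations and shifts.

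The documents do not support the stronger claims that the model is certainly unordered, that most items necessarily fail, or that a mean comparison always gains a fixed amount. The consequence is confined to secondary, item-level results; the primary outcome, the sum scores and the global rating do not depend on it.

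**What to change.** In Statistical analyses, replace the multinomial logistic GEE for single items by a comparison of mean item score between arms at team level: average each team's ratings, report the mean difference with its confidence interval, and refer it to t on 6 df. Show category counts by arm, and state that the items support the sum scores.

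This shares its target, a mean difference, with the linear GEE planned for the sum score, but the team-level t reference is new and should be stated as such. A team-level permutation test is an alternative. With 4 teams against 4 there are C(8,4) = 70 allocations, so the smallest two-sided p value is 2/70 = 0.029 and, without ties, the next is 4/70 = 0.057; only the most extreme split can reach 5%.

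The cost is one sentence and simpler code. Equal spacing of categories is assumed, as the sum score already does; category-specific odds ratios are lost; and item-level power stays modest.

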### The InterFACE tool

InterFACE was developed at the Geneva University Hospitals following an iterative user-centered process and ergonomic-driven approach by senior pediatric emergency physicians and nurses, computer scientists, software developers, and ergonomists with a strong background in medical app development. On the basis of pediatric resuscitation observations, AHA and ATLS guidelines, and focus groups, the team worked closely together to identify the key functionalities and processes to be implemented [38]. Both main components—the “Guiding Pad” app and the remote screen—are part of the whole shared decision-making tool intended to support and guide CPR providers during resuscitation, while improving team SA.

The “Guiding Pad” app was developed using Angular version 8, a development framework created by Google to build mobile and web apps. Assessment of this app and details regarding its functionalities have been described in a previous randomized trial [34]. In brief, the app displays a split screen with PALS algorithms split into interactive stages and adapted for tablet devices, as well as patient-centered cognitive aids to help with real-time decision-making (Fig. 3). The user can easily navigate through the algorithm in use and across the multiple algorithms at any time. For the purpose of the trial, no specific trauma guidelines will be implemented within the app. Indeed, the ATLS guidelines follow substantially the same didactic approach as outlined in the AHA guidelines for patients with primary cardiac arrest, with specific attention given to the technical support of vital functions with trauma-related equipment. Therefore, the app allows to select an exhaustive pre-defined and organized list of resuscitation materials and trauma-related equipment (and also symptoms and conditions that can be encountered during CPR). Finally, weight-based drug doses are automatically calculated by an on-board engine inherited from another evidence-based app [33].

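### If one arm of four teams has no dose or defibrillation errors, the planned Poisson GEE has no finite rate ratio and its usual Wald test is invalid

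*Protocol article*

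**What the plan says.** In the protocol article, Statistical analyses, a medication dose error is "a deviation from the correct weight dose of more than 10" per cent. The model for dose and defibrillation errors, treated as categorical, is then fixed: "A GEE model with a Poisson link will be used to assess the relationship between absolute errors in defibrillation and drug doses". The same section sets the level for all comparisons: "All statistical tests will be two-sided with a type I error risk of 5" per cent. It also plans to analyse absolute deviations and to report a mean difference with a 95% confidence interval.

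The number of clusters comes from Power and sample size calculation, where the total was "rounded up to 48 participants to obtain 8 teams of 6 participants per team". Group allocation specifies a "single, constant 1:1 allocation ratio", so about four teams per arm.

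The InterFACE tool section says that "weight-based drug doses are automatically calculated by an on-board engine". The background section on previous work reports fewer medication and defibrillation dose errors with the app in an earlier trial. In the first scenario, return of circulation is scripted to follow the fourth shock, so each team contributes only a handful of scored doses.

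The article names no variance estimator, test statistic or small-sample correction for this model. It gives no error rate for either arm.

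**The concern.** Dosing errors are team events, and there are only four teams on each side. When errors are rare, or when the tool largely prevents them, one arm may well record none. A log-link model then tries to estimate the logarithm of zero. Software usually still returns a coefficient, a standard error and a p value, and these depend on the variance estimator and on where the iterations stop, not on the evidence.

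What is at stake is the stated conclusion on dosing errors. Depending on the variance used, a single control-team error could be reported as overwhelming evidence for the tool, or a complete separation of the arms could be reported as no evidence at all.

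**Working it through.** **The plan's own figure.** The article gives no calculation for the error analysis. Its only sample-size figure is for the primary outcome, "90% power at a two-sided alpha level of 5" per cent for a "relative difference of at least 25% SA improvement between intervention groups" with SD 0.2. Taking the difference as 0.25, n per arm = 2 × (1.960 + 1.282)² × 0.2² / 0.25² = 13.5, so 14 as stated. Then 36 × 1.25 = 45, rounded to 48, and 48 / 6 = 8 teams. This reproduces, and it supplies the four clusters per arm used below.

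**Sandwich variance with an empty arm.** For each arm, the sandwich variance of the log rate is the sum of squared team residual totals divided by the square of the arm's fitted total.
- Arm with one error in four teams: the fitted total per team is 1/4 and the residuals are 3/4, −1/4, −1/4, −1/4. Variance = (9/16 + 3/16) / 1² = 0.75.
- Empty arm: the fitted total per team is a vanishing e and each residual is −e. Variance = 4e² / (4e)² = 0.25, however small e becomes.
- Sum = 1.00, so SE = 1.00 while the coefficient runs towards minus infinity.

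**Fitted results.** Poisson family, log link, independence working correlation, eight clusters of six binary rows, app v control:
- 0 v 1 error: b = −22.39, SE 1.00, p about 5e-111.
- 0 v 2 errors (two teams): b = −22.39, SE 0.71, p about 6e-220.

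The exact size of these p values is an artefact of where iteration stops. A separate fit in R, with a cluster sandwich computed by hand, stopped at b of about −18.5 to −18.9, still with SE 1.00. For 0 v 1, a bias-reduced sandwich gives SE 1.33, and p is still below 1e-50. A t reference on 6 degrees of freedom gives p of about 5e-7 (sandwich) to 4e-6 (bias-reduced).

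**Model-based variance.** This is the reciprocal of the fitted total in each arm, summed. The empty arm's fitted total is almost zero, so for 0 v 1 the SE is about 4e4 to 7e4 and p = 1.0. It stays at 1.0 when all four control teams err and no app team does.

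**Exact comparator.** If the split is forced to 4:4 there are C(8,4) = 70 allocations. With one error in each affected control team and none in the app arm, the two-sided p is:
- one team: 70/70 = 1.0
- two teams: 2 × C(6,2) / 70 = 30/70 = 0.43
- three teams: 2 × C(5,1) / 70 = 10/70 = 0.14
- four teams: 2/70 = 0.029

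**The failure is specific to the empty arm.** With one error in each arm the sandwich model gives p = 1.0, and 2 v 1 gives p = 0.49.

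**How often an arm would be empty.** Assume independent doses, the same error rate r in both arms and n doses per arm. Then P(exactly one arm empty) = 2q(1 − q), with q = (1 − r)^n. Neither r nor the number of scored doses is in the article.

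| Error rate r | 6 doses per team (n = 24) | 4 doses per team (n = 16) |
|---|---|---|
| 1% | 34% | 25% |
| 2% | 47% | 40% |
| 5% | 41% | 49% |
| 10% | 15% | 30% |
| 15% | 4% | 14% |
| 20% | 1% | 5% |

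For example, at 5% with n = 24, q = 0.95^24 = 0.292 and 2 × 0.292 × 0.708 = 0.41. Under the sandwich Wald test every such trial is a false rejection. Under model-based variance every such trial is a non-rejection, whatever the data show.

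**The case against.** The strongest reply is that the failing test is not in the document. The article names a GEE but neither the sandwich variance nor the Wald test, and both are choices that an analysis plan may settle. The result does depend on them: a generalised score test from the same GEE gives p = 0.285, 0.102, 0.028 and 0.005 for errors in one, two, three and four control teams against none. This stands in part. A reader might infer that the protocol as written commits the trial to declaring significance from one error; the text does not support that. It does fix a model whose ordinary Wald output is unusable under either common variance when an arm is empty. The score test avoids the collapse, but it rejects at three teams to none (0.028), where the exact p is 0.14.

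Four other stronger readings should be set aside.
- **A false-positive rate of 40% to 50%.** This holds only at low assumed error rates and under the sandwich Wald test. With six doses per team the empty-arm chance falls to 4% at a 15% error rate and 1% at 20%.
- **Automatic calculation makes zero app-arm errors likely.** It makes an empty arm plausible. However, the Medication dosage errors section also scores the delivered amount against the prescribed dose, so preparation and delivery errors remain possible. A zero caused by the tool would also be a real effect, whereas the table above assumes none.
- **This is the main safety outcome.** The article ranks no secondary outcome, and absolute deviations are analysed as well.
- **Seventy equally likely allocations.** The article states a 1:1 ratio but does not say that a 4:4 split is forced.

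**Conclusion.** The point holds as a conditional one. Given four teams per arm and a log-link Poisson GEE for categorical errors, an arm without errors leaves the rate ratio with no finite estimate and the usual Wald test invalid. For 0 v 1 error the sandwich version gives SE 1.00 and p far below 0.001 against an exact p of 1.0; the model-based version gives p of about 1.0 even for 0 v 4 teams. The usual small-sample corrections do not cure this.

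How often it would happen cannot be read from the document. It ranges from about 1% to nearly half of trials over error rates of 1% to 20% with four to six independent doses per team and no true effect. The sandwich variance and Wald test are assumed as the customary GEE output. The point concerns one analysis of a secondary outcome and leaves the primary situational awareness analysis untouched. It is worth changing because the case is foreseeable and the correction is cheap.

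**What to change.** In Statistical analyses, base the test of categorical dose and defibrillation errors on team-level error proportions, with an exact permutation test over the allocations that the randomisation allows (70 if the split is forced to 4:4). Report the risk difference. Give a GEE rate ratio only when both arms have at least one error, and replace the phrase Poisson link with Poisson family, log link.

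The cost is analysis wording only; no data collection changes. The downside is coarseness. With a 4:4 split the smallest two-sided p is 2/70 = 0.029 and the next possible value is 4/70 = 0.057, so at 5% the test rejects only when every team in one arm has a higher error proportion than every team in the other. That limit reflects having eight teams.
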